# Study Synopsis

| Title of clinical trial |  | Geriatrics and traumatology co-managing fragility fractures: effectiveness and success of implementation in a single centre setting |
| --- | --- | --- |
| Protocol Short Title/Acronym |  | G-COMAN FRACTURES |
| Sponsor name |  | UZ Leuven |
| Principal Investigator |  | [name] |
| Medical condition or disease under investigation |  | Older fragility fracture patients |
| Purpose of clinical trial |  | 1) To evaluate the effectiveness of a nurse-led geriatric-traumato co-management program using outcome indicators  2) To evaluate the feasibility of a nurse-led geriatric-traumato co-management program  2.1 To evaluate the reach and fidelity  2.2 To evaluate implementation targets 2.3 To evaluate implementation determinants  3)To evaluate the process of implementation of a nurse-led geriatric-traumato co-management program  3.1 To evaluate the reach and fidelity  3.2 To evaluate process outcomes |
| Primary objective |  | 1) Effectiveness evaluation: To determine if geriatric co-management is superior in preventing in-hospital complications |
| Secondary objective (s) |  | 1) Effectiveness evaluation: To determine if geriatric co-management is superior on following outcome indicators:  - length of stay  - unplanned readmissions within 30 and 90 days  - mortality  - functional status  - nutritional status  - quality of life  - falls and new fracture rate  - Discharge to a higher care level  - secondary fracture prevention started  - Cost-benefit of G-COMAN program  2) feasibility and process evaluation: To evaluate if geriatric co-management was successful implemented on the traumato ward:  -2.1 & 3.1: reach of the program and fidelity towards the core components of the care model  - 2.2: implementation targets  - 2.3: implementation determinants  -3.2: process outcomes:  * time to start physiotherapy  * time to start dietary advice  * use and duration of physical restraints  * use and duration of indwelling catheters (urinary tract catheter or intravenous catheter)  * Medication reconciliation at admission and discharge  * referral to geriatric day clinic  * referral to fracture liaison services |
| Trial Design |  | pre-post implementation study on the traumatology ward of the University Hospitals Leuven. |

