### 3.3 Secondary endpoints

1) Effectiveness evaluation

The secondary endpoints include comparison between the two groups on **patient outcome**:

- Length of hospital stay

- quality of life: EQ-5D^10^ (at admission, discharge, 1 month, 3 months, 6 months and 12 months post-surgery)

- functional status: Parker Mobility Score^11^, modified Barthel Index^12^, Lawton and Brody Scale^13^, Katz index (admission, discharge, 1 months, 3 months and 6 months post-surgery).

- hospital readmissions (30 and 90 days after discharge)

- falls (= “an unexpected event in which the patients comes to rest on the ground, floor or lower level”) and new fractures, either by retrospectively checking electronic patient record for any contact after discharge to any hospital or emergency department stating the occurrence of falls or new fractures) and by a questionnaire send out to patient and care givers. (admission, in-hospital, at discharge, at 1, 3, 6 months post-surgery 12 months post-surgery)

- Living situation: defined in 5 categories: living alone at home, living with spouse/partner, living with children, assisted living, living in a facility with 24h care such as nursing home). Details of care provided will be recorded as one of the following categories: 24h care, daily, irregular, no care. (admission, discharge, 1 month, 3 months post-surgery, 12 months after surgery)

- mortality (in-hospital, 1 month post-discharge and 12 months after discharge)

- secondary fracture prevention: documentation of fall risk assessment, medication review of calcium/vitamin D use and osteoporosis treatment, appointment to fracture liaison service (12 months after surgery)

- nutritional status: Mini Nutritional Assessment (MNA) ^14^ (at admission, 1 month, 3 months and 6 months post-surgery)

- cost-benefit analysis:

Costs will be assessed using a model that registers key hospital activities from the electronic patient record (KWS): 'beeldvorming', 'daghospitalisatie', 'dialyse', 'functiemeting', 'hospitalisatie', 'hospitalisatie ITE', 'labo', 'operatiekwartier', 'paramedische staf', 'raadpleging', 'raadpleging functiemeting', 'radiotherapie', 'spoedgevallen'. The model was developed by UHL.

2. Feasibility evaluation (is the intervention successfully implemented?):

2.1:

- the reach of the program (% of all eligible patients that were included in the G-COMAN program, defined as the patients who completed the questionnaire)

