### 3.4 Trial Design

single-centre pre-post implementation study on the traumatology ward of the University Hospitals Leuven

**Usual care (pre-cohort):** the control group receives usual care on the traumato ward. This means that the patient is cared for by a surgical resident. The interprofessional team furthermore consists of ward nurses, a physiotherapist, an occupational therapist and a social worker. No tailored geriatric protocols are available to the traumato team, except for those that are available hospital-wide for all patients (e.g. fall prevention, delirium). Geriatric expertise is available upon active request by the traumato team and includes the comprehensive evaluation of the patient by a geriatric nurse (consultation model).

Due to the design of the G-COMAN strategic project and its predefined strict timing schedule (a phased implementation with the need of a rapidly full implementation), the timeframe for inclusion of the pre-cohort is limited. At the end of the pre-cohort, the predefined sample size will not be reached. To obtain sufficient included patients in the pre-cohort, this patient cohort will be supplemented with patients of which retrospectively information will be gathered. This results in a pre-cohort that will be partly prospective and partly retrospective.

**Geriatric co-management intervention, quality-improvement project G-COMAN (post-cohort):** A dedicated traumato nurse (G-COMAN nurse) will systematically perform a frailty screening in all newly admitted older patients on the traumato ward to evaluate if they are to be included in the G-COMAN program. In eligible patients, a comprehensive geriatric assessment (CGA) will be performed by the G-COMAN nurse. Based on identified potential problems, a tailored care plan based on predefined geriatric protocols will be launched. As part of the project a geriatric specialist nurse will provide every weekday training and education of the G-COMAN nurse and other team members on the traumato ward. The implementation of automated care plans and predefined geriatric protocols will be coordinated by a G-COMAN project coordinator, as well as the organisation of focus groups and intervisions to ensure smooth and supported collaboration.

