In between pre-cohort and post-cohort, a single intervention group will be recruited as part of a feasibility study, in order to evaluate if the intervention is implemented successfully. If this is not the case, the implementation will be adapted and revaluation of successful implementation will be planned.

Due to the nature of the study design, health professionals and patients cannot be blinded. Blinding of outcome assessors is not considered feasible due to limited resources.

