### At discharge

The research assistant will monitor the incidence of complications using patient assessment (4AT) and by monitoring the patients record throughout hospitalization, and will assess the outcomes on hospital discharge using patient interview. **Discharge date, medication and mortality** will be evaluated based on the electronic patient record. **Functional status** is measured using the Parker Mobility Score^11^, Barthel Index ^12^, Katz index and Lawton and Brody scale based on reports, if possible from the patient, from next of kin or from nursing staff. **Quality of life** will be evaluated using the EQ-5D questionnaire. **Fall history** will be evaluated using a questionnaire. **Cognition** will be assessed using the Mini-cog test. **Living situation** will be defined within the next 5 categories: living alone at their own home, living with a spouse/partner at their own home, living with children or sibling, living in assisted living facility, living in a facility with 24u care (nursing home, rehabilitation setting,…). Details of care provided will be recorded as one of the following categories: 24h care, daily, irregular, no care. Variables that can be retrospectively collected are as follows: discharge date, medication, mortality, fall history and living situation.

Also **several process outcomes** of the G-COMAN program will be evaluated using registrations in the electronic patient records and by patient interviews: reach of the program (% of eligible patients that were effectively enrolled into the program), fidelity to the program (% of patients included in G-COMAN traumatology program who had a screening or assessment focusing on *delirium, nutritional status, pressure ulcer risk* using a validated tool within 48h of admission to traumatology ward) and specific care process; such as the *time to start physiotherapy*; *time to start dietary advice*; use, *type and duration of fixation;* *use, duration and reason of indwelling catheters (urinary tract catheter or intravenous catheter); medication reconciliation; referral to geriatric day clinic* for follow-up; *and referral to a fracture liaison service (Zoledronate infusion or metabolic bone consultation).*

*Cost-benefit will be calculated by UHL financial division using the UHL cost model based on retrospective data collected at least 3 months post-discharge.*

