Feasibility study: Analysis of the feasibility/process indicators will be reported as frequencies and proportions for categorical data and as mean and standard deviation for continuous data. Qualitative data (focus groups and interviews) will be analysed using a thematic analysis. Two researchers will independently code the data using Word-documents. Integration of quantitative data and qualitative data will occur via embedding by linking data collection and analysis at multiple points.

We are aware of following risk of bias: lack of randomization might induce bias due to the influence of uncontrolled or unbalanced variables. Risk of bias due to death, loss of follow-up or uncompliant patients unable to complete questionnaires is possible. In the latter case, caretakers might help complete the questionnaires if feasible.

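### Nurses who deliver the programme may supply the discharge functional scores in the post-cohort, and the protocol does not require the informant to be recorded

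*Protocol*

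**What the plan says.** Functional status is one of the secondary outcomes in the Study Synopsis, under the objective "To determine if geriatric co-management is superior on following outcome indicators". Section 3.3 makes discharge a comparison time point: "Katz index (admission, discharge, 1 months, 3 months and 6 months post-surgery".

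Section 5.1, At discharge, says that the research assistant "will assess the outcomes on hospital discharge using patient interview". It then allows the four functional scales to be "based on reports, if possible from the patient, from next of kin or from nursing staff". It does not say which nursing staff.

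Section 3.4 describes who delivers the programme. "A dedicated traumato nurse (G-COMAN nurse) will systematically perform a frailty screening", and in eligible patients the same nurse performs the CGA. A geriatric specialist nurse will "provide every weekday training and education of the G-COMAN nurse and other team members on the traumato ward". Several fidelity items in 3.3 are ward nursing tasks. In the pre-cohort, ward nurses give usual care and geriatric expertise comes only on request.

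On blinding, 3.4 states that patients and professionals are unblinded and adds: "Blinding of outcome assessors is not considered feasible due to limited resources". The only remark on proxy reporting is in 8.2: "caretakers might help complete the questionnaires if feasible". Neither the flowchart in 3.6 nor the visit descriptions in 5.1 list the informant as a variable.

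**The concern.** The words *nursing staff* mean different things in the two cohorts. Before implementation they are usual-care nurses. Afterwards they include the nurse who performed the CGA, a specialist nurse employed to promote the programme, and ward colleagues trained in it. If these informants describe function differently from their predecessors, the measurement error differs between cohorts and enters the discharge comparison as a programme effect.

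Nurse reports are most likely for patients who cannot answer, for example because of delirium. Delirium is a component of the primary endpoint, so a programme that works could itself change the mix of informants.

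If the informant is not recorded at the time, no later analysis plan can examine the problem. At stake is a superiority statement on function at discharge; the primary endpoint is not touched.

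**Working it through.** **Textual check**

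| Question | What the protocol gives |
| --- | --- |
| Who assesses at discharge? | The research assistant (5.1) |
| Who may supply the report? | Patient if possible, next of kin, nursing staff (5.1) |
| Are programme nurses excluded as a source? | No |
| Do nurses deliver the programme? | Yes (3.4; fidelity items in 3.3) |
| Must the informant be recorded? | Not stated in 3.6 or 5.1 |
| Is discharge function available for retrospective controls? | No: baseline only (3.6), and not among the retrospective discharge variables (5.1) |

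The last row means that the discharge comparison rests on prospective controls only. Section 3.4 says that the prospective pre-cohort will fall short of the planned size, without giving its number.

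**Size, under assumptions**

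The protocol states no figure on this point, so there is none to reproduce. From the protocol: 108 per group with about 5% loss (8.1), so 108 × 0.95 = 102.6, about 103 evaluable; and the 0-100 range of the modified Barthel Index (3.6). Assumed, because the protocol does not give them:

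- share q of discharge scores reported by nurses: 0.20 to 0.40;
- shift d in nurse-reported scores, post-cohort relative to pre-cohort: 5 to 10 Barthel points;
- SD: 20 to 25 points;
- prospective controls n₁: 50, with 103 as the ceiling; post-cohort n₂ = 103;
- no true effect.

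Formulas:

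- bias = q × d, from 0.20 × 5 = 1.0 to 0.40 × 10 = 4.0 points;
- SE = SD × √(1/n₁ + 1/n₂);
- error rate = P(|Z + bias/SE| > 1.96).

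| n₁ / n₂ | SD | SE | Bias | Bias/SE | Error rate |
| --- | --- | --- | --- | --- | --- |
| 50 / 103 | 25 | 4.31 | 1.0 | 0.23 | 5.6% |
| 50 / 103 | 25 | 4.31 | 4.0 | 0.93 | 15.3% |
| 50 / 103 | 20 | 3.45 | 1.0 | 0.29 | 6.0% |
| 50 / 103 | 20 | 3.45 | 4.0 | 1.16 | 21.3% |
| 103 / 103 | 25 | 3.48 | 1.5 (q = 0.30, d = 5) | 0.43 | 7.2% |
| 103 / 103 | 20 | 2.79 | 4.0 | 1.44 | 30.0% |

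With 50 controls the range is 5.6% to 21.3%. The 30% row combines the largest share, the largest shift, the smallest SD and a full complement of prospective controls, which 3.4 itself rules out.

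**The case against.** **The intervention team does not rate the endpoint.** A reader might infer that programme staff score their own outcome. The protocol does not support this. The research assistant assesses, the patient is preferred where possible, and nursing staff come last of the three sources. Nothing says that the G-COMAN nurse will be the one asked. This stands: the point is only that programme nurses may supply the content of the report.

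**Unblinded assessment is already disclosed.** True, and patients' own reports carry expectation bias too. But the disclosure concerns assessors, and the remark in 8.2 concerns caretakers. Neither covers programme staff as informants, and restricting or recording the informant needs no blinded assessor.

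**The size is assumed.** This stands. The middle case (30% nurse reports, 5 points, SD 25, 103 per group) gives only about 7%. The direction is also open: a nurse who has done a CGA may know of more dependence, which would bias against the programme.

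**Adjusting for the informant would not cure it.** This also stands. The feared shift is an informant-by-cohort interaction, which a main-effect covariate leaves in place. Informant type arises after exposure, so conditioning on it can compare different kinds of patients in the two cohorts.

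**It is too late for the pre-cohort.** Largely true. Section 4.3 schedules pre-cohort inclusion from October 2021 to March 2022, and the Synopsis dates Amendment 2 to 22-04-2022. New rules can act only on the post-cohort, scheduled from September 2022. Barring the two programme roles there still brings the cohorts closer together, since neither role existed in usual care.

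**The case report form may hold the field.** Possibly; the form is not shown. The protocol does not require it.

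A reader might also extend the point to 1, 3 and 6 months. There patients or care givers complete questionnaires under the same procedure in both cohorts, so the argument about programme nurses is confined to discharge.

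**Conclusion.** The point holds in a limited form. At one time point of a secondary superiority outcome, nurses delivering the programme may be the source of the score in the post-cohort, and the protocol does not require the informant to be recorded. The possibility of differential error follows from the text; its size and direction do not. With an assumed 50 prospective controls and the assumed ranges above, the 5% error rate would become about 6% to 21%. A 30% error rate should not be read as an expectation. The change is worth making because it is cheap and because an unrecorded informant may not be recoverable later.

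**What to change.** **Section 5.1.** State that patient, next of kin and nursing staff form an order of preference, and that the G-COMAN nurse and the geriatric specialist nurse may not be the informant. Record the informant at each functional assessment in the post-cohort. For the prospective pre-cohort, enter it where source notes show it.

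**Section 8.2.** Add a sensitivity analysis that repeats the discharge comparison without nurse-reported scores. Note that informant type is measured after exposure and may differ between cohorts. For that reason it should not be a covariate in the main model, and the sensitivity result needs the same caution.

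**Cost.** One REDCap field and a few sentences. A few more discharge scores will be missing where only a barred nurse could have reported, and pre-cohort informant data will be incomplete. Trained ward nurses remain possible informants, so the bias is reduced but not removed.

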- use and duration of physical restraints (as registered in the electronic patient record; 3-points fixation or higher degrees of fixation)

- use and duration of indwelling catheters (urinary tract catheter or intravenous catheter as registered in the electronic patient record)

- Medication reconciliation at admission and discharge (calcium/vitamin D supplements and AOM)

- referral to geriatric day clinic (appointment to E459 in the year following first admission)

- Referral to fracture liaison services (Zoledronate infusion and/or metabolic bone consultation)

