| Quality of life | EQ-5D | Mobility, self-care, daily activities, pain, anxiety |  | Questionnaire | X | X | X | X | X | X | No |
| Medication | N/A | Use of calcium/Vitamin D supplements and/or  anti-osteoporotic medication  Polypharmacy (≥ 5 medications) |  | Questionnaire  record | X | X | X | X | X | X | Only baseline and discharge via record |
| Falls and fractures history | N/A | Fall = “an unexpected event in which the patient comes to rest on the ground, floor or lower level” |  | Questionnaire  Record | X | X | X | X | X | X | Only baseline and discharge via record |

M = month, FU = follow-up.

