***Process outcomes in the prospective pre- and post-cohort and retrospective pre-cohort.***

| **Variable** | **Instrument** | **Description** | **Score** | **Type of assessment** | **Prospective pre-cohort/post-cohort** | | | | | | **Retrospective pre-cohort** |
| --- | --- | --- | --- | --- | --- | --- | --- | --- | --- | --- | --- |
|  |  |  |  |  | **Admission** | **Discharge** | **1M FU** | **3M FU** | **6M FU** | **12M FU** | **Yes/No** |
| Reach | NA | Only post-cohort: Number of eligible patients included within G-COMAN | NA | NA |  | X |  |  |  |  | Yes |
| Fidelity | NA | Only post-cohort: Number of patients receiving the core components of G-COMAN | NA | NA |  | X |  |  |  |  | Yes |
| Physical therapy | NA | Number of patients receiving physiotherapy  Numbers of days until start physiotherapy | NA | NA |  | X |  |  |  |  | Yes |
| Dietary advice | NA | Number of patients receiving dietary advice  Number of days until start of dietary advice | NA | NA |  | X |  |  |  |  | Yes |
| Physical restraints | NA | Number of patients being restrained  Duration of the use of restraints  Type of restraints used | NA | NA |  | X |  |  |  |  | Yes |
| Indwelling catheters | NA | Number of patients with an indwelling catheter (urinary tract catheter or intravenous catheter)  Duration of catheterization  Reason for catheterization | NA | NA |  | X |  |  |  |  | Yes |
| Medication reconcilliation | NA | Number of patients with calcium/vitamin D supplements and/or AOM | NA | NA |  | X |  |  |  |  | Yes |
| Referral to geriatric outpatient clinic at discharge | NA | Number of patients referred to the falls clinic, memory clinic, follow up | NA | NA |  | X |  |  |  |  | Yes |
| Referral to FLS | NA | Number of patients referred for Zoledronate infusion or metabolic bone consultation | NA | NA |  | X |  |  |  |  | Yes |

M = months, FU = follow-up.

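### In-hospital falls are collected with a patient questionnaire in prospective patients but from the record alone in retrospective controls, so ascertainment differs between the compared cohorts

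*Protocol*

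**What the plan says.** **Falls.** Protocol 3.3 lists falls among the patient outcomes to be compared between the two groups, at these time points: "admission, in-hospital, at discharge, at 1, 3, 6 months post-surgery 12 months post-surgery". The hospital stay is therefore covered. The sources named there are the electronic record and a questionnaire. In 5.1 (At discharge), fall history "will be evaluated using a questionnaire", and fall history is also listed among the items that can be collected retrospectively. In the flowchart (3.6), the falls row gives questionnaire and record as the types of assessment, with a mark at discharge for prospective patients. For the retrospective pre-cohort the same row reads "Only baseline and discharge via record".

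**Composition of the groups.** Section 3.4 explains that the control group will be filled up with retrospective patients: "This results in a pre-cohort that will be partly prospective and partly retrospective". No retrospective part is planned for the post-cohort.

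**Process outcomes.** Section 5.1 (At discharge) says that several process outcomes "will be evaluated using registrations in the electronic patient records and by patient interviews". Its list runs from reach and fidelity to physiotherapy, dietary advice, fixation, catheters and referrals. Section 3.3 defines restraint use more narrowly: "use and duration of physical restraints (as registered in the electronic patient record; 3-points fixation or higher degrees of fixation".

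**The concern.** A fall on the ward that the patient or a relative reports, but that nobody registered, can be counted in every post-cohort patient and in prospective controls. It cannot be counted in a retrospective control. The two groups then differ in how falls are looked for as well as in the care they received.

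This is a different matter from post-discharge falls. There the flowchart shows openly that retrospective controls have no value. For the hospital stay every patient has a value, so the data can be pooled and the difference in source will not be visible. Section 8.2 gives generic between-group tests for secondary outcomes and does not separate retrospective from prospective controls. The covariates it lists for the complications model are patient characteristics, and adjusting for those cannot correct a difference in measurement. The biases acknowledged at the end of 8.2 do not include differential ascertainment.

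At stake is the reading of one secondary endpoint: a true reduction in in-hospital falls could be masked, or an apparent increase produced.

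**Working it through.** **1. Sources for falls up to discharge, side by side**

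| Place in the Protocol | Prospective pre-cohort and post-cohort | Retrospective pre-cohort |
| --- | --- | --- |
| 3.3 | record and questionnaire | not separated |
| 3.6, falls row | questionnaire and record | record only |
| 5.1, At discharge | questionnaire | listed as retrospectively collectable |

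The questionnaire exists for all post-cohort patients and for only part of the controls. This follows from the text without any assumption.

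**2. What it could do to the comparison**

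The plan has no figure of its own to reproduce here. It does not state the fall risk, the retrospective share or the completeness of the record. The 108 per group in 8.1 is sized on complications and serves below only as a denominator. Everything in this step is illustration.

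Let p be the fall risk as found by record and questionnaire together, equal in both groups. Let r be the retrospective share of controls, and s the fraction of those falls that the record holds.

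- Observed post-cohort risk = p
- Observed control risk = p × [1 − r(1 − s)]
- Apparent ratio, post versus pre, under no effect = 1 / [1 − r(1 − s)]

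With r = 0.5:

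| s | Control capture | Apparent ratio |
| --- | --- | --- |
| 0.8 | 1 − 0.5 × 0.2 = 0.90 | 1.11 |
| 0.7 | 1 − 0.5 × 0.3 = 0.85 | 1.18 |
| 0.6 | 1 − 0.5 × 0.4 = 0.80 | 1.25 |

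With r from 0.3 to 0.7 and s from 0.6 to 0.9, the ends of the range are 1/(1 − 0.3 × 0.1) = 1/0.97 = 1.03 and 1/(1 − 0.7 × 0.4) = 1/0.72 = 1.39.

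In absolute terms the deficit in controls is p × r × (1 − s):

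- p = 10%, r = 0.5, s = 0.8: 1.0 percentage point, so 9.0% against 10.0%. In 108 patients this is 9.7 against 10.8, about one patient.
- p = 5%, r = 0.25, s = 0.8: 0.25 points.
- p = 20%, r = 0.75, s = 0.6: 6.0 points.

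**3. Is the direction certain?**

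The formulas above assume that prospective patients have both sources, as the flowchart row suggests. Section 5.1 names only the questionnaire at discharge. If that is the sole source in practice, let q be the fraction of all true falls that the questionnaire finds, and now let s be the fraction of all true falls in the record. The observed difference (post minus pre) under no effect is then q·p − p[(1 − r)q + r·s] = p·r·(q − s). Its sign depends on which source is the more complete, and the documents do not say.

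**4. Restraints and other process outcomes**

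Section 3.3 ties restraints, catheters and time to physiotherapy to what is registered in the record. The process-outcome table in 3.6, whose restraint row begins "Number of patients being restrained", gives no type of assessment and marks the item as available retrospectively without restriction. Only the general sentence in 5.1 adds interviews, and it does not say for which items. Under the 3.3 definition both groups share one source. Under 5.1 they might not.

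**The case against.** The strongest case against has four parts.

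- **Restraint use.** A reader might infer from 5.1 that restraint use is under-counted in controls. The documents do not support that. The endpoint definition in 3.3 rests on the record, and the interview wording covers a long list without assigning interviews to any item. The only process indicators that 8.2 names, under the feasibility study, are to be described and not tested. What remains is a conflict of wording. This objection stands.
- **Direction for falls.** A reader might also infer that control falls are certainly under-counted. In 3.3 the record search is described for contacts after discharge. Section 5.1 names only a questionnaire at discharge, and at baseline fall history refers to the time before the injury. The sign is therefore likely if the questionnaire comes on top of the record, but it is not established. This also stands.
- **Size.** Every input to the ratios is assumed, and 1.39 pairs two extremes. The middle example moves about one patient in 108. This stands as well, so no ratio should be quoted as a finding.
- **Openness and place.** The mixed cohort and its record-only sources are declared, and the analysis could be refined in a statistical analysis plan that is not at hand. This does not remove the point. The unequal source is fixed by the Protocol's own collection rules, and its stated risks of bias do not mention it.

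**Conclusion.** The point holds for in-hospital falls. The Protocol gives prospective patients a questionnaire that retrospective controls lack, and only the control group contains retrospective patients. If the questionnaire adds to the record, the comparison is biased against the programme. The size is unknown: the illustrative range is 0.25 to 6.0 percentage points, wholly dependent on the assumed risk (5% to 20%), record capture (60% to 80%) and retrospective share (25% to 75%).

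For restraints, catheters and time to physiotherapy the finding is only that 5.1 and 3.3 disagree about the source. These are secondary and process outcomes, so the primary endpoint and the 108 per group are not touched. The change is still worth making because it costs little and removes an avoidable difference between the cohorts.

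**What to change.** - In 3.3 and 8.2, state that the between-cohort comparison of in-hospital falls uses record-registered falls in all pre- and post-cohort patients. The record search in 3.3 should explicitly cover the index stay.
- Use questionnaire-reported in-hospital falls only in a secondary comparison of prospective pre-cohort with post-cohort patients.
- In 5.1 (At discharge), reconcile the mention of interviews with the record-based definitions in 3.3, so that compared process outcomes such as restraints, catheters and time to physiotherapy use the record in both cohorts. If interviews serve particular items, name them.

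The cost is wording. The record is already a listed source for falls, and 5.1 already has the research assistant follow each prospective patient's record through the stay. The downside is that falls reported only by patients or relatives drop out of the main comparison, so absolute rates will be slightly lower. A common source also does not guard against a change over time in how completely the ward registers falls; that limit should be acknowledged when the result is reported.
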